## Secondary endpoints

• Changes in symptom burden assessed by the Seattle Angina Questionnaire (SAQ)

• Changes in biomarkers including inflammatory markers and markers of metabolism

• Changes in exercise capacity (VO_2_peak)

• Changes in body weight and fat distribution (DEXA scan)

• Changes in level of anxiety and depression (HADS questionnaire)

• Changes in systolic and diastolic heart function at rest and during stress including advanced imaging (eg. Strain-Echocardiography)

## Figure 3. Project plan milestones

## Study participants

### Inclusion criteria

Patients will be recruited and included from the ongoing iPower study (please see figure 2)^28^ i.e.

- - Female gender
  - 40-75 years of age
  - Referred to a cardiac centre for assessment with coronary angiography due to chest pain or other signs of ischemia leaving out ST-segment elevation myocardial Infarction (STEMI) or NSTEMI patients (elevated enzymes, electrocardiographic (ECG) changes/no ECG changes)
  - No significant stenotic lesions at the following CAG defined as > 50% stenosis of epicardial vessels. Patients are included from the PATS database within 1 year after coronary angiography.
- Angina with a symptom burden of symptoms > monthly
- Impaired coronary microvascular function, defined as a TTDE measured CFVR < 2.5 with a good quality (quality index > 3)
- BMI > 25 (for BMI < 26 waist hip ratio must be > 0.8)
- Informed consent

### Exclusion criteria

- Previously verified MI, verified in medical records: STEMI, elevated coronary markers^2^ or NSTEMI
- Previous percutaneous coronary intervention or coronary artery bypass graft.
- Left ventricular ejection fraction (LVEF) < 45% assessed by echocardiography within 6 months before inclusion
- Any allergies to the content of the LED (gluten/nuts), allergy to dipyridamole, adenosine, or teofyllamine
- Significant valvular heart disease^[[1]](#footnote-1)^
- Congenital heart disease
- Severe asthma
- Severe chronic obstructive pulmonary disease (COPD): FEV1 < 50% of predicted (age, height, ethnicity)
- Severe comorbidity with limited life-expectancy < 1 year
- Chest pain with a strongly suspected non-ischemic etiology (e.g. pericarditis, pneumonia)
- Pregnancy
- Active cancer
- Severe renal failure (eGFR < 30) or severe hepatic comorbidity
- Chronic alcohol abuse
- Atrial flutter or fibrillation
- Atrioventricular block > 1^st^ degree
- Diabetes Mellitus type I
- Participation in other trials if relevant for the present study
- Language- or other barrier to giving informed consent
- Physical or mental disabilities contraindicating or hampering diet or exercise training
- Travel distance to research hospital requiring more than 3 hours of travel, making it difficult for the patient to participate

### Withdrawal criteria

- Sudden unexpected serious adverse reaction or sustained side effects
- Poor compliance with LED, training or medicine compliance defined in the methodology chapter.

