# Aims

The aim of this study is a ‘proof-of-concept’, i.e. to determine whether a comprehensive

intervention is feasible and results in improvement in both angina and CMD.

The study is a pilot study which we, if successful, will seek to expand to a multicenter interventional trial with prognostic outcome in collaboration with an international

consortium.

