## Randomization

A third party unrelated to the study will perform randomization of participants with randomly permuted block sizes of 2,4, and 6 using the ralloc program in Stata 11. Replacement of participants will be possible in case of dropout.

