## Figure 4. Participants’ study plan

## Figure 5. Antihypertensive treatment algorithm

### Exercise training (ET)

ET consists of group sessions of aerobic interval training and resistance exercise, scheduled twice weekly throughout the 24-week intervention period. Each group consists of 10 participants and each session lasts for 1 h. The group sessions are supervised and monitored by a physiotherapist experienced in cardiac rehabilitation. The intensity of the training will be individually adapted to the concomitant weight loss program with restricted calorie intake. During the first 12 weeks of calorie restriction, the training will be modest in load and intensity and primarily consist of short aerobic interval sessions and resistance exercise of the large muscle groups.

Attendance at training sessions will be registered by the physiotherapist. Home based training is accepted, if participants cannot attend all the sessions. Compliance of home-based training is self-reported (registered by a telephone call to the participant). Lack of compliance is defined as < 50% attendance to training sessions/home training. Lack of compliance within the first five weeks of intervention will lead to withdrawal from the study and possibly new inclusion.

**Please see Figure 6** for an overview of the estimated timeline of the training sessions throughout the study period. The 30 participants in the intervention group attend at 3 teams of 10 participants.

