### Low energy diet (LED)

Weight loss will be achieved by following an evidence-based LED formula delivered by Cambridge Weight Plan. The diet, consisting of shakes, soups and bars, allows the participant to consume 800-1200 kcal/day. The diet contains the daily need of energy as well as macro- and micronutrients, proteins, essential fatty acids and recommended daily doses of vitamins and minerals^29^. The goal of the intervention is a total weight loss of at least 10% without significant loss of muscle mass.

Participants will be offered comprehensive support to fulfill the weight loss through a combination of two individual meetings and group sessions with a dietician. Attendance in a group session (5-7 participants and a dietician) defines the beginning of the 24-week interventional period for each participant. The purpose of this meeting is information about the LED treatment. Hereafter, participants are offered a single individual meeting with the dietician in order to register weight and dispense the Cambridge Weight Plan diet. Participants then follow a 12-week period with LED and attend group sessions every second week with their team and a dietician. The purpose of the group sessions is to motivate, adjust treatment to individual concerns, and monitor weight and compliance to intervention. During the 12^th^ week, participants will be offered another individual meeting with the dietician in order to motivate and advise in the weight maintenance diet.

The recommended weight maintenance diet is high in protein and with a low glycemic index modified from the DiOGenes study.^30^ Taking into consideration that the participants have CMD the high protein diet is adapted to resemble the Mediterranean diet, which is low in saturated fat (< 10%) and recommended to heart patients,^31^ with protein sources mainly from fish, poultry, egg, dairy, and vegetables. During the 12 weeks of weight maintenance the participants will be encouraged to still attend the monthly group sessions with the dietician. In case of weight gain LED can be used to replace meals. No weight loss within the first three weeks of LED is considered as lack of compliance and leads to withdrawal from the study.

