# Statistics

## Sample size

The primary endpoint is change in microvascular function assessed by CFVR.

We wish to be able to detect a difference in change in CFVR between groups of 10%, equal to a change in CFVR of 0.24, assuming a baseline mean CFVR of 2.4. According to our previous study (22) the standard deviation of the within individual change is assumed to be 0.3. With power of 0.8 and two-sided significance level of 0.05, 26 patients should be included in each group. With 26 in each patient group we will be able to detect a moderate or larger effect on symptom burden. Anticipating dropout, randomization of a total of 60 patients was chosen. Dropout within the first three weeks of inclusion is replaced by new inclusion.

SAQ has four subscales each with a score from 1-100. We have not found data on within-study subject variation on SAQ. However, previous trials have obtained changes in SAQ of 10-20 points after intervention.^18^ ^46^ ^13^ A trial of 46 patients (predominantly women) with microvascular angina randomized to either ranolazine, ivabradine or placebo for four weeks found a SAQ score change of 10-40 points across different SAQ parameters, all highly significant (p<0.001).^18^ We will conduct a study on a similar study population, and we therefore expect to have the statistical power to document clinically relevant effects.

With 60 participants included, the probability is 80 percent that the study will detect a treatment difference at a two-sided 0.05 significance level, if the true difference between treatments is 11. This is based on the assumption that the standard deviation of the response variable is 15.

Analyses will be performed in STATA/IC 13.1. Categorical data will be presented as number (percentage), continuous data as mean (SD) or median (interquartile range) if normal distribution cannot be assumed. Regression analysis will be performed with the primary outcome change in symptoms (SAQ) and the independent variable change in CFVR.

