# Risks and disadvantage for participants

According to previous trials, patients with microvessel disease have an increased risk of cardiovascular mortality and morbidity. To date no approved treatment for microvessel disease exists. This study may add to the understanding of microvessel disease and possible treatment options with a direct effect on the microvasculature. By improving microvessel function the progression of cardiovascular disease may be prevented in these patients. At the individual level, participants randomized to intervention in this study will hopefully benefit from the comprehensive support and treatment team towards a more heart-healthy lifestyle and increased quality of life. By this intervention it is possible for participants to improve their physical condition, achieve fat reduction, especially the visceral fat surrounding the heart and other vital organs and thereby reduce risk factors for cardiac disease, among these hypertension, diabetes and metabolic syndrome. Risks and disadvantages are considered offset by the potential benefits of the study.

Expected disadvantages are discomfort/pain in relation to blood testing, risk of following rash or bruises that are considered harmless and will disappear after a few days.

Adenosine, which might be used during the CFVR measurements instead of dipyridamole, has known side effects similar to dipyridamole. Adenosine side effects are observed more frequently, however, they normally last for only one minute. In case of severe disadvantage for the participant in relation to infusion of adenosine an antidote, Teofyllamine, will be given. Hereafter symptoms usually diminish within minutes.

Exercise training will be monitored by a physiotherapist with experience in cardiac rehabilitation. There will be supportive health educated staff in the building in case of emergency as well as resuscitation equipment. Participating in exercise training is considered safe.

The low calorie diet with Cambridge Weight Plan has been used in studies of overweight patients without being associated with health risk.^52^ The diet intervention will be guided by a clinical dietician experienced in cardiac rehabilitation.

By Dexa scan the participant is exposed to a radiation dose of about 0.005 mSv which is considered insignificant. In comparison the annual background radiation in Denmark is

2 - 20 mSv depending on location.

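### Harm is a withdrawal criterion with no week-24 follow-up provided, and no common adverse-event recording is described for two arms with very unequal contact

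*Protocol*

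**What the plan says.** Under Withdrawal criteria the protocol gives two reasons. One is harm: "Sudden unexpected serious adverse reaction or sustained side effects". The other is compliance: "Poor compliance with LED, training or medicine compliance defined in the methodology chapter". The section does not say whether withdrawal is from treatment or from the study.

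For compliance, other sections do say. Exercise training (ET): "Lack of compliance within the first five weeks of intervention will lead to withdrawal from the study and possibly new inclusion". Low energy diet (LED): "No weight loss within the first three weeks of LED is considered as lack of compliance and leads to withdrawal from the study".

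Replacement is provided for in several places. Randomization: "Replacement of participants will be possible in case of dropout", with no time limit. Sample size: "Dropout within the first three weeks of inclusion is replaced by new inclusion". Table 3 budgets for ten additional women for this purpose.

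Table 1 schedules outcome assessments at baseline and week 24 only. It has no adverse-event row, and harms are not among the primary or secondary endpoints. The risk section lists expected discomforts and the safety cover during training and testing, but no recording procedure.

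The Aims section asks whether the intervention is feasible and improves angina and microvascular function. The investigators "if successful, will seek to expand to a multicenter interventional trial with prognostic outcome".

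**The concern.** Nothing in the protocol brings a woman withdrawn for harm back at week 24 for CFVR, the Seattle Angina Questionnaire (SAQ), DEXA or blood tests, or follows her for later events. Read with the compliance and replacement rules, she can leave and another woman may be enrolled.

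The loss is unlikely to be even. Diet and supervised training are given only to the intervention arm, so most reactions to them would fall there. The week-24 comparison would then set women who tolerated the package against nearly all controls. Women who cannot tolerate the package are also direct evidence on feasibility, on which the step to a larger trial rests. Body composition shows the point: the protocol treats loss of lean mass as a risk to be watched, yet the only DEXA after baseline is at week 24, so a woman who leaves has none.

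The second part is recording. With no common harm question, reports would arise spontaneously, and one arm meets staff far more often than the other.

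This is not a matter that an analysis plan can settle later. Who is followed and what is asked at visits are conduct rules, and measurements never taken cannot be recovered.

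**Working it through.** **1. The plan's own sample size.** Inputs from Sample size: difference 0.24, SD of change 0.3, two-sided alpha 0.05, power 0.80.

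- Normal approximation: n = 2 × [0.3 × (1.960 + 0.842) / 0.24]² = 24.5, so 25 per group.
- Two-sample t-test: 25.5, so 26 per group, which is the stated figure. Power at 26 per group is 0.807.
- 60 randomised against 2 × 26 = 52 needed leaves 8, or 8/60 = 13.3%, four per arm.

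The sample size reproduces and is not at fault.

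**2. What unbalanced loss could do to the estimate.** The protocol gives no rate of withdrawal for harm, so this is an illustration. Assume w of the 30 intervention women are withdrawn for harm, all 30 controls stay, completers gain 0.24 over controls, and withdrawn women gain g. The effect in all randomised women is then 0.24 × (1 − w/30) + g × w/30.

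| w | Completer-only power (t-test) | g = 0 | g = 0.12 | g = 0.24 |
|---|---|---|---|---|
| 0 | 0.861 | 0.240 | 0.240 | 0.240 |
| 2 | 0.849 | 0.224 | 0.232 | 0.240 |
| 4 | 0.835 | 0.208 | 0.224 | 0.240 |
| 6 | 0.818 | 0.192 | 0.216 | 0.240 |

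For w = 4 and g = 0: 0.24 × 26/30 = 0.208. Completer power hardly moves; the issue is which women the estimate describes. There is no bias if the withdrawn women gain as much as completers.

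**3. Scheduled contact** (Exercise training, Low energy diet, Methods, Controls – usual care).

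- Intervention: training 2 × 24 = 48; diet groups at weeks 0, 1, 3, 5, 7, 9 and 11 = 7; monthly groups in weeks 12 to 24, taken as 3; individual diet meetings 2. Sum: 48 + 7 + 3 + 2 = 60. This is an upper figure, because home training registered by telephone may replace sessions.
- Controls: baseline and follow-up, plus blood pressure and LDL monitoring through the study for those who need medication. Two is therefore a minimum.

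**4. The replacement rules side by side.**

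| Section | Rule |
|---|---|
| Randomization | Replacement possible on dropout, no time limit |
| Exercise training | Withdrawal for poor compliance in the first five weeks, replacement possible |
| Low energy diet | Withdrawal if no weight is lost in the first three weeks, replacement not mentioned |
| Sample size | Dropout in the first three weeks is replaced |

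These differ in window and in whether replacement is optional. None says how the replaced woman is kept in the report.

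**The case against.** The harm criterion does not itself say that the woman leaves the study; that wording belongs to the compliance rules. This is correct. The reading is plausible, not stated, and the ambiguity is a reason to clarify.

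A reader might infer that harms are collected on unequal terms by design. The documents do not support that. They describe no collection rule in either arm; unequal reporting is an inference from unequal contact. Nor is the contrast simply 60 to 2, given home training on one side and medication monitoring on the other. Controls on medication could also meet the harm criterion.

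A reader might also infer that harmed women vanish from the harm count, so that one or two events in 30 (3.3% or 6.7%) become none. That does not follow. A reaction that triggers withdrawal is known when it happens, Data storage keeps every patient's data under her study number, and no rule puts a replacement in her place in a count. What may be lost is the later course, later events and the week-24 measurements. The upper limit for zero events in 30, 1 − 0.05^(1/30) = 9.5%, follows from the arm size and would hold under perfect follow-up.

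Table 1 does schedule medical history, ECG, blood tests and DEXA at week 24 in both arms, which helps for women who attend. The statement "Risks and disadvantages are considered offset by the potential benefits of the study" is a prospective ethical judgement, not a result the trial claims to test. Which reactions should trigger the criterion is a clinical matter and forms no part of this point.

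**Conclusion.** The point holds in a limited form. The protocol makes harm a reason for withdrawal, provides no follow-up afterwards, allows replacement, and describes no adverse-event recording in either arm. Followed as written, it lets harm-related loss, probably concentrated in the intervention arm, select the women with week-24 data.

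The size cannot be fixed from the documents. With four intervention women lost, the gap between completers and all randomised women runs from nothing to 0.032 (0.24 − 0.208). This assumes that no controls are lost and that the withdrawn women gain between nothing and as much as completers; it would be larger if they ended up worse than controls. The conclusion also assumes that withdrawal for harm means leaving the study, as it does for compliance. How missing outcomes are analysed may be set out in an analysis plan not shown and is not counted here.

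This is a worthwhile, inexpensive improvement. It does not show that the trial's harm data would be void or that the sample size is wrong.

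**What to change.** - State under Withdrawal criteria that meeting the harm criterion does not end study participation. When treatment should be stopped is left to the sponsor.
- Invite every randomised woman to the week-24 assessments, subject to her consent.
- Keep withdrawn women in the record and in the report by randomised arm, even if a replacement is enrolled.
- Reconcile the replacement wording in Randomization, Exercise training and Sample size.
- Ask the same fixed harm questions in both arms in the medical-history slot already scheduled at week 24, by telephone for those who do not attend. Report the answers by randomised arm, and tabulate separately any reports that arise only at training or diet contacts.

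The cost is some wording, one short form and a few calls. The measured effect may be diluted: if four women gained nothing, the all-randomised effect of 0.208 would have power of about 0.75 with 30 per arm, against 0.861 for 0.24.

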# Methods

Sixty participants are included, examined at baseline and randomized (1:1) to either comprehensive treatment or usual care (controls). Comprehensive treatment consists of 24 weeks of LED, exercise training and optimized medical treatment. Usual care is medical treatment handled by the researcher, MD, at baseline and follow-up. In case of delay, e.g. cancellation of appointments by the participants, four weeks are accepted between baseline assessments and start of intervention (week 0, defined by the first (baseline-) meeting with dietician). A delay of up to four weeks (eg. cancellation) is accepted.

## Blinding

- Blinding of participants and investigators to treatment allocation is not possible due to the study setup.
- All baseline assessments will be conducted before randomization.
- Reading of the primary outcome CFVR and TTSDE at follow-up will be blinded.
- VO_2_max test at follow-up will be blinded to the conducting physiotherapist.
- DEXA scan at follow-up will be blinded to the conducting MD.

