## Figure 2. Flowchart of the study

## Table 1. Schematic overview of data assessments

| **Table 1** | Time (min) | **Baseline**  **Week 0** | | | **Follow-up**  **Week 24** | | |
| --- | --- | --- | --- | --- | --- | --- | --- |
|  |  | stud med | MD | physio | stud med | MD | physio |
| Informed consent | 10 | x |  |  |  |  |  |
| In- and exclusion criteria |  |  |  |  |  |  |  |
| General health examination |  |  |  |  |  |  |  |
| Medical history | 10 | x |  |  | x |  |  |
| ECG | 10 | x |  |  | x |  |  |
| Blood pressure, heart rate, BMI, anthropometry, ECG | 15 | x |  |  | x |  |  |
| Blood samples |  |  |  |  |  |  |  |
| Haematology, lipids, liver, kidney and endocrine function (TSH, glucose, hbA1c, inflammatory markers) | 10 | x |  |  | x |  |  |
| Questionnaires |  |  |  |  |  |  |  |
| HADS | 10 | x |  |  | x |  |  |
| SAQ | 10 | x |  |  | x |  |  |
| Ultrasound tests |  |  |  |  |  |  |  |
| Echocardiography (TTDE) | 40 |  | x |  |  | x |  |
| Coronary flow reserve (CFVR) | 60 |  | x |  |  | x |  |
| Stress echocardiography | 20 |  | x |  |  | x |  |
| Fat distribution and physical test |  |  |  |  |  |  |  |
| DEXA scan | 40 | x |  |  | x |  |  |
| VO_2_max test | 60 |  |  | x |  |  | x |
| Time consumption (hours) |  | ~5 | | 1 |  | | 1 |

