## Table 2. Overview of the components of the 24-week intervention

|  | Target group | Duration | Intervention | sessions | Goal | Responsible |
| --- | --- | --- | --- | --- | --- | --- |
| **Exercise training**  **Week 0-24** | **All** | **1½ h** | **Twice a week** | **Group** | **VO_2_ peak 10% improved** | **Card rehab team: Physiotherapist** |
| **Weight loss**  **Week 0-12** | **All** | **1 h** | **Every second week**  **+**  **1 individual** | **Group**  **+**  **individual** | **10% weight loss** | **Card rehab team: Dietician** |
| **Weight maintenance**  **Week 12-24** | **All** | **1 h** | **Monthly**  **+**  **1 individual** | **Group**  **+**  **individual** | **Heart healthy diet** | **Card rehab team: Dietician** |
| **Smoking cessation** | **Smokers**  **33%** |  | **Pharmacological support** | **Group** | **Quit smoking** | **MUNICIPAL** |
| **Optimized medication** | **LDL > 2**  **SBT >130**  **HbA1c >6.0^*^** | **½ h** | **Statin**  **ACE blocker**  **Metformin** | **Individual** | **LDL < 2**  **BP 130/80**  **HbA1c < 6.5** | **Clinical assistant, MD** |

^*^ Newly diagnosed DM2

##

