# Costs

## Table 3. Overview of estimated costs of the 24-week intervention

| **24-week intervention** | **Item in intervention** | **Time (hours)** | **Salary/hour** | **Costs (DKK)** |
| --- | --- | --- | --- | --- |
| ET group sessions (physio) | 3h/week x 24 weeks x 3 teams of 8 participants | 216 | 200 | 43.200 |
| VO_2_max test (CPET) baseline + follow-up (physio) | 45 min/participant x 130* | 97½ | 200 | 19.500 |
| LED group sessions (dietician) | 1 h x 6 teams x 9 times | 54 | 254 | 13.716 |
| Weight registration e.g.  (dietician) | ½ h x 54 times | 27 | 254 | 6.858 |
| Weight loss individual sessions (dietician) | 1 h/participant x 70* times | 70 | 254 | 17.780 |
| Cambridge Weight Plan Diet | 3 meals daily x 12 weeks x 70 participants* | 0 | Sponsored | 0 |
| Smoking cessation group sessions (nurse) | 3 sessions x 1 h  (10 participants) | 0 | Municipal | 0 |
| **Total costs, all patients** |  |  |  | **101.054** |

*10 participants extra in case of drop-out and new inclusion. CPET includes control group participants.*

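### Only the reading of the follow-up CFVR is blinded, not its acquisition, and the DEXA blind names a role that does not run the scan

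*Protocol*

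**What the plan says.** The Blinding section of the protocol opens by stating that "Blinding of participants and investigators to treatment allocation is not possible due to the study setup" and that "All baseline assessments will be conducted before randomization". It then gives three blinds for follow-up:

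- **CFVR and stress echo:** "Reading of the primary outcome CFVR and TTSDE at follow-up will be blinded".
- **VO2max test:** blinded to the physiotherapist who conducts it.
- **DEXA:** "DEXA scan at follow-up will be blinded to the conducting MD".

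Table 1 shows who performs each assessment. Its columns at baseline and week 24 are "stud med | MD | physio | stud med | MD | physio". The row "Coronary flow reserve (CFVR) | 60" is marked under MD at both visits, as are echocardiography and stress echocardiography. DEXA is marked under the medical student at both visits, and the VO2max test under the physiotherapist.

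On treatment, Table 2 makes the "Clinical assistant, MD" responsible for optimised medication in the intervention arm. The Methods opening and the section on controls have the researcher MD handle medical treatment of the usual-care arm. The Exercise training section has a physiotherapist supervise the twice-weekly sessions. Table 3 costs "VO_2_max test (CPET) baseline + follow-up (physio") as a physiotherapist task.

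**The concern.** For VO2max and DEXA, the blind is written for the person who conducts the test. For the primary endpoint, it is written only for the reading. A blinded reader works from the recordings that the operator obtained and kept. If the operator knows the arm, that knowledge can affect how long a good signal is sought, whether a run is repeated, and which recordings reach the reader. Blinded reading does not undo any of these choices.

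The DEXA line has a different fault. A blind that names a role other than the operator protects nobody who touches the measurement. For CPET, participants are encouraged to continue to exhaustion, so the tester's knowledge of the woman matters. The text does not say that tester and trainer are different people.

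At stake is how far the primary result of an open-label trial can be described as assessed without knowledge of treatment.

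**Working it through.** **1. The sections side by side (follow-up visit)**

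| Measurement | Blind stated in Blinding | Operator in Table 1 | Same type of staff also treats or trains? | Result |
| --- | --- | --- | --- | --- |
| CFVR (primary) | Reading only | MD | Yes: MDs manage medication in both arms | Acquisition has no stated blind; scanner and treating MD not separated |
| DEXA | Conducting MD | Medical student | Not stated | Blind and operator do not match |
| VO2max (CPET) | Conducting physiotherapist | Physiotherapist | Yes: a physiotherapist supervises training | Blind and operator match; separation from the trainer not stated |

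Baseline assessments precede randomization, so the exposure is confined to follow-up.

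**2. The plan's own figure**

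Inputs from Sample size: difference 0.24, SD of change 0.3, power 0.8, two-sided 0.05, 1:1 allocation.

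- Normal approximation: n per group = 2 × (1.960 + 0.842)² × (0.3 / 0.24)² = 2 × 7.85 × 1.5625 = 24.5, rounded up to 25.
- t-test solution: 25.5, rounded up to 26, with power 80.7% at 26 per group and 86.1% at 30.

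The stated 26 per group is reproduced. The point about blinding changes no design figure.

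**3. What a given bias would do**

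The documents give no acquisition bias, so the values below are assumptions. Let *b* be a net difference between arms in mean CFVR change that comes only from acquisition. A shift that is equal in both arms cancels. With 26 per arm, the standard error of the difference is 0.3 × √(2/26) = 0.083, so *b* = 0.05 is 0.6 standard errors and *b* = 0.10 is 1.2. Rejection rates of the two-sided 5% t-test when the true effect is zero:

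| Assumed *b* | As % of baseline 2.4 | 26 per arm | 30 per arm |
| --- | --- | --- | --- |
| 0 | 0 | 5.0% | 5.0% |
| 0.02 | 0.8% | 5.6% | 5.7% |
| 0.05 | 2.1% | 9.1% | 9.7% |
| 0.10 | 4.2% | 21.8% | 24.6% |
| 0.12 | 5.0% | 29.3% | 33.2% |

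The rates are the same whichever arm the shift favours. The table shows how sensitive the test is to a small systematic shift. It is no evidence that such a shift would occur.

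**The case against.** The strongest reply is that the protocol is candid. It says that participants and investigators are unblinded, limits its CFVR claim to reading, and measures baseline before randomization. Blinded reading is a recognised safeguard in an open-label lifestyle trial, so asking for protected acquisition as well is an improvement to a design choice rather than the correction of a false statement. That stands, and it limits the weight of the CFVR part. It does not answer the DEXA mismatch.

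Four stronger readings are tempting, and the documents do not support them.

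- *The scanning MD is the treating MD.* A reader might infer this from the shared job label. The protocol speaks of an MD, a clinical assistant MD, a researcher MD and, under Intervention, doctors in the plural. It neither identifies nor separates them. The statement about unblinded investigators does not settle it, because the same list blinds a conducting MD and a conducting physiotherapist.
- *The CPET blind contradicts the staffing.* Blinding and Table 1 both name a physiotherapist. Table 2 gives VO2 peak only as a training goal, Table 3 is a cost line, and Intervention refers to physiotherapists in the plural. A second physiotherapist would satisfy the text.
- *Acquisition is the variable step.* The CFVR procedure section reports highly reproducible reading by two observers in 50 iPower patients, and an 11% within-subject coefficient of variation for repeat examinations in another, overweight population. The 11% covers the whole examination, including real change between visits, and reproducibility was better within a week. The same section gives 7% for same-observer repeats in 10 healthy subjects. The comparison does not locate the variability in acquisition.
- *The 11% sets a scale for the bias.* At a CFVR of 2.4 it is 0.11 × 2.4 = 0.26, but that is random variation in one woman's examination. The target of 0.24 is a difference between group means. A random error of that kind says nothing about the size of a systematic one.

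**Conclusion.** The point holds in a limited form. As written, acquisition and selection of the primary endpoint's follow-up recordings are open to an operator who may know the allocation. The DEXA blind is assigned to a role that Table 1 does not give the scan to, which is a plain inconsistency. For CPET there is only an unstated separation.

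The size of any CFVR bias cannot be derived from the documents, and nothing in them shows that it would favour the intervention. The only quantitative statement available is conditional: on the protocol's SD of 0.3, with 26 per arm and no true effect, a net shift of 0.05 or 0.10 would bring the false-positive rate to about 9% or 22%. Blinded reading and pre-randomization baseline both limit the exposure. The change is still worth making, because the safeguard is nearly free and the blinded reader is already planned. The sample size is unaffected.

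**What to change.** Revise the Blinding section as follows.

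1. Store all rest and stress recordings from the follow-up CFVR examination and pass them, unselected and anonymised, to the blinded reader, who selects the beats.
2. Allow a repeat run only on the quality index, which the inclusion criteria already use, and not on the CFVR value obtained.
3. With existing staff and where possible, roster the follow-up CFVR scan to an MD who is not treating that woman, and the follow-up CPET to a physiotherapist who has not trained her. Where this is not possible, report that acquisition was unblinded.
4. Reconcile the DEXA line with Table 1 so that the blind applies to the role that runs the scan.

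The cost is protocol wording, some image storage and some scheduling work. The first two steps need no change in who scans.
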